### Data collection and management

2.7

Before the start of treatment, 7 days after the start of the treatment, and at the end of the treatment, collect data according to the evaluation criteria. 28 days after the end of the treatment, each patient will be followed up by outpatient or telephone. The detailed record of the follow-up information cannot be collected. Two assistants cooperate to collect. Personal information about potential participants and registered participants will be collected, shared and stored in an independent storage room to protect confidentiality before, during and after the test. Access to the database is limited to researchers in this research group.

### Statistical analysis

2.8

In this study, SPSS25.0 statistical analysis software is used for data analysis, and the measurement data is represented by ($\bar{x}\pm s$); For data conforming to normality and homogeneity of variance, the group *t* test is used between groups, and the paired *t* test is used within the group; the rank sum test is used for those that does not conform to the normal distribution; the Chi-Squared test is used for count data. *P* < .05 is statistically significant.

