### Sample Size Calculation

2.4

This study is a pilot clinical trial. Based on the analysis and calculation of the relevant literature published in the past 10 years, the efficiency of western medicine is 75.47%, and the effective rate of Chinese medicine combined with western medicine is 96.23%. The sample content estimation formula is used for comparison of multiple sample rates. Set the significance test level α = 0.05, then μ_α_ = 1.96, 1-β = 0.9, μ_β_ = 1.28, δ = π1-π2. The sample content estimation formula for comparing 2 sample rates: $N_{1}=N_{2}={\left(\frac{\mu_{\alpha }+\mu_{\beta }}{\delta }\right)}^{2}[\pi_{1}(1-\pi_{1})+\pi_{2}(1-\pi_{2})]$

The calculated sample size of each group is 54 cases. Considering factors such as shedding, it is expanded by about 20%, and 130 patients need to be included. According to the order of visits, the random number method was used to divide the patients into a control group and an observation group, with 65 cases in each group.

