### Study design

2.5

This study will recruit patients who come to the outpatient clinic to screen and happen to meet the criteria. The patients and their families will approve the study plan and sign an informed consent form. The patients are randomly assigned to the treatment group and the control group. Among them, the treatment group is given Buyang Huanwu decoction (Radix Astragali seu Hedysari 30 g, Lumbricus 6 g, Flos Carthami 6 g, Radix Paeoniae Rubra 10 g, Radix Angelicae Sinensis 10 g, Semen Persicae 6 g, and Rhizoma Ligustici Chuanxiong 6 g), 1 bag at a time (180 ml), twice a day; The control group is given a placebo. The packaging, color, taste, dosage form and size of the placebo are exactly the same as the treatment group. The 2 groups of patients will receive the same routine care and basic treatment, control the patient's blood sugar, blood pressure, blood lipids, etc., and receive health education. If necessary, the attending doctor can adjust the plan according to the patient's condition. All intervention methods will be recorded in detail. Used for final result analysis.^[15]^ We will set up a dedicated drug administrator, and the nurse will be responsible for preparing drugs. Therefore, this study is not blind to nurses, but to researchers, patients and statisticians. All patients will receive 14 days of treatment. Before and after treatment and on the 7th day of treatment, the health status of each patient will be assessed, including efficacy indicators and safety indicators, and all patients will be followed up for 28 days by telephone. Follow-up content includes cardiovascular events and rehospitalization.

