### Evaluation criteria and judgment of curative effect

2.6

1.Main observation indicators: Venous Clinical Severity Score; Venous Dysfunction Score^[16]^; TCM Syndrome Points;2.Secondary observation indicators: Aberdeen Varicose Vein Questionnaire; Hemorheology indicators (including whole blood viscosity, plasma viscosity, hematocrit, fibrinogen and erythrocyte sedimentation rate (ESR));3.Adverse reactions: Including abnormal liver function and any uncomfortable symptoms (such as dizziness, nausea, etc.) during treatment.

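### Section 2.8 compares the arms without adjusting for the baseline scores it collects, and does not say whether final scores or changes are compared; ANCOVA would gain precision at no cost

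*Protocol article*

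**What the plan says.** Section 2.8 (Statistical analysis) names the methods for continuous data. Between arms: "For data conforming to normality and homogeneity of variance, the group *t* test is used between groups". Inside each arm: "the paired *t* test is used within the group". Otherwise: "the rank sum test is used for those that does not conform to the normal distribution". No covariate appears in any of these.

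The baseline values exist. Section 2.5, in its account of treatment and assessments, says "Before and after treatment and on the 7th day of treatment, the health status of each patient will be assessed", and includes the efficacy outcomes in that assessment. Section 2.7 gives the same three time points.

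The main outcomes in section 2.6 are scores: "Main observation indicators: Venous Clinical Severity Score; Venous Dysfunction Score", together with the TCM syndrome points. AVVQ and the haemorheology measures are secondary and are also numerical.

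**The concern.** Three things are left in a weak state by what section 2.8 does say.

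- **Baseline is not used to compare the arms.** It enters explicitly only through the paired test within each arm, which says nothing about the difference between arms. Where baseline and final scores are correlated, a comparison of final scores leaves explainable variation in the error term.
- **The dependent variable is not stated.** The group t test could be run on end-of-treatment scores or on changes from baseline. These have different variances and can give different answers on the same data.
- **The test is picked from the data, and the rule has a gap.** Normal data with equal variances go to the t test and non-normal data to the rank sum test. Normal data with unequal variances go to neither. One score may therefore be reported as a mean difference and the next as a rank comparison.

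At stake is precision on the three main scores, and having one effect measure per score settled before the data are seen.

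**Working it through.** **Inputs from the protocol article.** Section 2.4: "Set the significance test level α = 0.05, then μ_α_ = 1.96" (so two-sided); "1-β = 0.9, μ_β_ = 1.28"; effective rates 75.47% and 96.23%; 54 per group; about 20% added; 65 per group, 130 in total.

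**Inputs assumed.** The document gives no SD, target difference or baseline correlation for any score. I take a standardised mean difference (SMD) d, centred on 0.5 and varied from 0.3 to 0.6, and a baseline-to-final correlation ρ of 0.3, 0.5 and 0.7, with equal SDs at both times.

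**Step 1: the plan's own figure.** δ = 0.9623 − 0.7547 = 0.2076. Then ((1.96 + 1.28)/0.2076)² × [0.7547 × 0.2453 + 0.9623 × 0.0377] = 243.6 × 0.2214 = 53.93, rounded up to 54. Next, 54 × 1.2 = 64.8, so 65 per group. Both figures reproduce. They concern a binary rate, not the scores.

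**Step 2: variance of each analysis, relative to a t test on final scores (= 1).**

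| Analysis | Formula | ρ = 0.3 | ρ = 0.5 | ρ = 0.7 |
|---|---|---|---|---|
| t test on change | 2(1 − ρ) | 1.40 | 1.00 | 0.60 |
| ANCOVA | 1 − ρ² | 0.91 | 0.75 | 0.51 |

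The ratio of ANCOVA to change is (1 − ρ²)/(2(1 − ρ)) = (1 + ρ)/2, which is below 1 for any ρ below 1. So ANCOVA beats both t tests whenever 0 < ρ < 1. At ρ = 0 it gains nothing over the final-score test.

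**Step 3: power.** Power ≈ Φ( d × √(n/2) / √(variance factor) − 1.96 ). For n = 54 and d = 0.5, d × √(n/2) = 0.5 × √27 = 2.598.

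- Final scores: Φ(2.598 − 1.96) = 73.8%.
- ANCOVA at ρ = 0.5: Φ(2.598/0.866 − 1.96) = Φ(1.04) = 85.1%.

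| n per arm, d = 0.5 | Analysis | ρ = 0.3 | ρ = 0.5 | ρ = 0.7 |
|---|---|---|---|---|
| 54 | t test, final | 73.8% | 73.8% | 73.8% |
| 54 | t test, change | 59.3% | 73.8% | 91.8% |
| 54 | ANCOVA | 77.7% | 85.1% | 95.3% |
| 65 | t test, final | 81.3% | 81.3% | 81.3% |
| 65 | t test, change | 67.3% | 81.3% | 95.7% |
| 65 | ANCOVA | 84.8% | 90.8% | 97.9% |

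Power from the t distribution at 54 per arm is slightly lower: 73.1% unadjusted, and 84.4% and 95.0% for ANCOVA at ρ = 0.5 and 0.7.

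**Step 4: other effect sizes at 54 per arm.**

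| d | t test, final | ANCOVA at ρ = 0.3 / 0.5 / 0.7 |
|---|---|---|
| 0.3 | 34.4% | 37.2% / 43.6% / 58.8% |
| 0.4 | 54.7% | 58.7% / 67.0% / 82.9% |
| 0.6 | 87.7% | 90.5% / 95.0% / 99.2% |

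**Step 5: the same gain as patients.** ANCOVA matches the precision of 54 per arm unadjusted with 54(1 − ρ²) = 49.1, 40.5 and 27.5, that is about 50, 41 and 28 per arm at the three correlations.

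**Step 6: the distribution check.** A simulation with 54 per arm and 4,000 runs per scenario chose t or rank sum by a Shapiro-Wilk test in each arm; it did not gate on equal variance. Type I error of the gated choice was 0.042 to 0.053. With normal data and d = 0.5, its power was 0.73, like the t test, against 0.83 and 0.95 for ANCOVA at ρ = 0.5 and 0.7. With skewed (lognormal) data and a shift of 0.5 SD, its power was 0.97, against 0.76 for the t test and 0.84 to 0.93 for linear ANCOVA.

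**The case against.** The strongest reply is that the stated tests are valid, that the trial calls itself a pilot, and that a condensed article leaves covariates, confidence intervals and standard-error choices to an analysis plan that is not shown. Much of this stands. The absence of those details is not held against the article. What remains is that section 2.8 names a definite between-arm method, and that method has no baseline term.

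Four stronger readings are tempting, and the document does not support them.

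- **That the trial falls short of power it needs.** The 90% in section 2.4 is for a binary effective rate. No power target is stated for the scores, so none is shown to be missed. An unadjusted t test has 90% power at d of about 0.62 with 54 per arm and about 0.57 with 65.
- **That baseline is ignored altogether.** This is so only if final scores are compared. A test on change uses baseline, though less efficiently. At ρ = 0.7 it is only 3.5 points below ANCOVA with 54 per arm (91.8% against 95.3%).
- **That chance baseline imbalance biases the result.** Randomisation keeps the unadjusted estimate unbiased, and its standard error already covers such imbalance. With 65 per arm, the baseline difference has a standard error of √(2/65) = 0.175 SD, so 1.96 × 0.175 = 0.34 SD is within ordinary chance. For final scores it carries through at about ρ times its size, or 0.17 SD at ρ = 0.5. That is a matter of precision. How widely baseline scores will vary is not reported.
- **That choosing the test by a normality check inflates error or costs power.** It did neither in the scenarios run. For skewed scores the gated choice had more power than linear ANCOVA. What stands against it is that the quantity estimated is not fixed in advance.

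**Conclusion.** The point holds as one of efficiency and specification. The planned between-arm tests are valid, but they leave out a covariate that is already collected, leave open whether final scores or changes are compared, and give no rule for normal data with unequal variances.

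For roughly normal scores with 0 < ρ < 1, ANCOVA is more precise than either form of the t test. Over ρ from 0.3 to 0.7 at d = 0.5, the gain over a final-score test is about 4 to 22 percentage points of power with 54 per arm and about 4 to 17 with 65. Over a change-score test with 54 per arm, it is about 18, 11 and 4 points at ρ = 0.3, 0.5 and 0.7. These sizes rest on assumed ρ and d and on approximate normality. The document does not allow the real gain to be fixed, and for strongly skewed scores a rank-based test could do better than linear ANCOVA.

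**What to change.** Make the primary between-group analysis of VCSS, VDS and TCM points an ANCOVA of the day-14 value on treatment group and that score's own baseline. Do the same for AVVQ and the haemorheology measures. Report the adjusted mean difference with its 95% confidence interval and heteroscedasticity-robust standard errors, which also closes the gap for unequal variances.

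Fix this in advance in place of a choice made by a normality check. Keep a rank-based analysis (rank sum, or rank ANCOVA with baseline) as a pre-specified sensitivity analysis, since it can be more powerful if the scores are strongly skewed.

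The cost is a change of wording before unblinding. It needs no new data, visits or patients, and ANCOVA is available in SPSS, the software the protocol already names.

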## Discussion

3

The clinical manifestations of varicose veins of the lower extremities are chronic venous insufficiency (CVI), the main symptoms are varicose veins, edema, skin pigmentation and ulcers, etc.,^[17]^ it is a common type of disease in vascular surgery,^[18]^ more common in all parts of the world.^[19]^ Varicose veins of the lower extremities often occur in workers or standing for a long time, and its risk factors include pregnancy, smoking, and overweight.^[20]^ The veins of the lower extremities are equipped with effective tube walls, contracted vascular smooth muscles and qualified valves to withstand pressure and allow deoxygenated blood to flow to the heart in 1 direction.^[21]^ When some factors cause it to exceed the body's own regulation, it will manifest as symptoms such as varicose veins in the lower limbs. If effective methods are not taken, it will lead to the occurrence of ulcers in the lower limbs, which not only affects the health of the patient, but also greatly reduces their quality of lives.^[22]^ Surgery is the most common method for the treatment of varicose veins of the lower extremities. The clinical effect is definite,^[23]^ but patients are prone to various complications after operation, such as lower extremity phlebitis, lower extremity venous thrombosis, etc.,^[24,25]^ which seriously affect the quality of life of patients, and even threaten life safety, so it is of great significance to find other suitable treatment methods.

Traditional Chinese medicine treatment of varicose veins of the lower extremities is mainly based on blood circulation and stasis removal drugs.^[26]^ But Buyang Huanwu decoction has the effect of replenishing Qi and activating blood. Modern pharmacological studies have found that Buyang Huanwu decoction has the effects of inducing angiogenesis, inhibiting cell apoptosis, and protecting nerves.^[27–29]^ It can significantly increase the levels of element binding protein and vascular endothelial growth factor, and significantly reduce inflammation,^[30,31]^ at the same time has the effect of anti-atherosclerosis,^[32,33]^ it can be seen that Buyang Huanwu decoction can play its unique advantages in treating patients with varicose veins of the lower extremities, and has fewer adverse reactions.

This randomized controlled trial is to verify that Buyang Huanwu decoction can significantly improve the clinical symptoms of patients with varicose veins and improve vascular function. Since there is no high-quality randomized controlled trial to evaluate the efficacy and safety of Buyang Huanwu decoction for patients with varicose veins of the lower limbs, it is very meaningful for us to carry out this study.
